### Recruitment, randomisation and blinding

Where the appropriate consent was obtained and baseline assessment completed, the researchers randomised participants sequentially via an automated system at the Clinical Trials Research Unit (CTRU) at the University of Leeds. Participants were randomly allocated on a 1:1 basis to receive FT or TAU, using a computer-generated minimisation programme incorporating a random element to ensure the treatment arms were well balanced for the following: centre (CAMHS team), gender, age (11 to 14 or 15 to 17), living arrangements (with parents or guardians/foster care), number of previous self-harm episodes (including index event) (2 or ≥ 3), and type of index episode (self-poisoning, self-injury, or combination). Where therapists were not aligned to a specific service but covered a number of services, additional randomisation of the lead therapist took place within the FT team in order to minimise case-selection bias.

Participants and therapists were, of necessity, aware of treatment allocation, but researchers were blind to the allocation to allow unbiased collection of follow-up data. CTRU was responsible for informing CAMHS clinicians and family therapists of randomisation outcome, to maintain researcher blinding.

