### Follow-up

The primary outcome measure was obtained from Accident and Emergency Departments (A&E) and in-patient Hospital Episode Statistic (HES) data downloads from the NHS Health and Social Care Information Centre (HSCIC), which holds hospital attendance and admission data for hospitals across England. This method of primary outcome data collection was augmented by directed hospital record searches, undertaken by researchers at frequent intervals throughout the trial. Researchers searched Acute Trust records for episode details that were unclear from the central HES data, or for any hospital attendances for those participants who had not consented to the trial team providing their details to the HSCIC. Given that HES data sets are England-wide, this maximised collection of hospital attendance data, allowing for participants moving out of catchment area (within England). Collection of these routine data also minimised bias by eliminating the possibility of preferential researcher data collection at certain Acute Trusts.

Postal questionnaires were administered by CTRU at 3 and 6 months post-randomisation. If questionnaires were not returned, postal reminders were sent 2 weeks after the initial mailing and then again a further 2 weeks later.

Secondary outcome were obtained via face-to-face researcher interviews at 12 and 18 months following randomisation.

Data relating to treatment were provided by the treating CAMHS clinicians or Family Therapists, Clinical Studies Officers (CSOs) employed by the Research Networks in each locality and by the researchers, when blinding was no longer required (that is, after participant-reported follow-up data had been collected). The data included session attendance (FT and TAU), therapeutic approach (for TAU), referrals within and outside CAMHS, requirements for psychotropic medications, and liaison with other agencies. In addition, treating clinicians and participants completed the System for Observing Family Therapy Alliances scale (SOFTA) [44] at the end of the third treatment session. Supervision sessions for Family Therapists, and routinely provided clinical supervision for CAMHS clinicians were also recorded.

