### Primary endpoint analysis

Cox’s Proportional Hazards Model accounting for the minimisation factors will be used to test for differences in 18-month repetition rates. Hazard Ratios and corresponding 95 % confidence intervals (CIs) will be presented. If a participant is lost to follow-up, they will be treated as censored. Kaplan-Meier curves will be constructed for each group and compared using a two-sided log-rank test. Although the significance level has been slightly reduced to account for an interim analysis, CIs will still be presented at the 95 % level. The extent of clustering on participant outcomes due to therapists and the impact on the precision of the treatment effect estimate will be investigated using multilevel survival frailty models in a secondary analysis. Sensitivity analysis will also be used to assess the impact of missing details of hospital attendance should they remain by the time of analysis (that is, where it is unclear whether an attendance was due to self-harm or not).

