
### Clinical service engagement

During the early stages of implementation of the trial CAMH Services were slow to engage with SHIFT. We deemed the slow initial recruitment a consequence of clinical unfamiliarity with research in many sites, the pressures of routine clinical practice and the sheer size of the task of involving so many clinicians in trial processes. The nature of the trial was such that anyone within the clinical team undertaking referral assessments could consider a young person’s eligibility for the trial and then be involved in TAU delivery. Ensuring all clinicians were fully informed about trial processes and had the research materials available was logistically complex. Very regular contact between the trial team and local services facilitated a collaborative and flexible approach, and was helped by the appointment of local trial ‘champions’ who took a lead in reminding their local colleagues of trial procedures. This process took the form of newsletters circulated by CTRU, posters for staff rooms and formal presentations delivered at research or team events. In addition, a training DVD was produced in which the Chief Investigator, researchers and trial therapists discussed the salient points of the trial in a short explanatory piece designed for clinicians.

Data collection from a large number of clinicians was not straightforward as there was little opportunity for learning on the clinicians’ part, a TAU clinician might only see one or two SHIFT participants over the duration of the trial so there is opportunity for missing data. Data collection (from clinicians) was thus a labour intensive task, and was ultimately superseded by data collection by researchers (where they could be un-blinded – for example, at the end of follow-up) and by Clinical Research Networks’ Clinical Studies Officers.

Despite the complexity of SHIFT, the trial ultimately recruited well, following implementation of intensive measures to improve screening and recruitment in 2010 after a slow start in 2009, and was able to complete recruitment at the end of 2013 following an extension award by HTA.

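### Researcher blinding is released on completion of participant-reported data, so late hospital-record searches that feed the primary endpoint may be done unblinded

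*Protocol article*

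**What the plan says.** All references are to the protocol article.

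- **Purpose of blinding.** Recruitment, randomisation and blinding says that "researchers were blind to the allocation to allow unbiased collection of follow-up data". It makes no exception for hospital-record data.
- **Source of the primary endpoint.** Follow-up names A&E data and "in-patient Hospital Episode Statistic (HES) data downloads from the NHS Health and Social Care Information Centre (HSCIC". This source is "augmented by directed hospital record searches, undertaken by researchers at frequent intervals throughout the trial".
- **What the searches cover.** "Researchers searched Acute Trust records for episode details that were unclear from the central HES data". They also cover any attendances of participants who had not agreed to their details going to HSCIC.
- **Release of the blind.** The same section lists who supplies treatment data, including session attendance in each arm and the therapeutic approach under TAU. Researchers are on that list "when blinding was no longer required (that is, after participant-reported follow-up data had been collected".
- **Practice.** Clinical service engagement reports that treatment-data collection from clinicians was eventually "superseded by data collection by researchers (where they could be un-blinded – for example, at the end of follow-up", and by Clinical Studies Officers.
- **Ambiguity of cause.** Primary endpoint analysis plans a sensitivity analysis for details still missing at analysis, "where it is unclear whether an attendance was due to self-harm or not".

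**The concern.** The release rule names a milestone that has nothing to do with the primary endpoint. Trial objectives and outcomes explains that this endpoint was chosen partly because it does not depend on self-report. Completing participant-reported follow-up therefore says nothing about whether the endpoint data are complete. Once that milestone passes, a researcher may read a participant's session records, learn the arm, and still have record searches outstanding for the same participant.

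That an attendance took place is objective. Its cause is not always clear, as the article accepts. A researcher who knows the arm could search harder, or record ambiguous detail differently, in one arm than in the other. Whoever then classifies the attendance works from what was found and recorded. Any such difference would act directly on the primary hazard ratio. The planned sensitivity analysis would not show it, because it covers attendances still unclear at analysis and not those already resolved by someone unblinded.

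**Working it through.** **1. Does the rule cover the primary endpoint?**

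| Data | Source | Protected by the release rule? |
|---|---|---|
| Interview and questionnaire outcomes | Participant-reported | Yes, blinding holds until they are collected |
| Attendances clear in HES | Central download | Does not depend on researcher blinding |
| Attendances unclear in HES | Researcher search of Acute Trust records | Only if searched before release |
| Any attendance, no HSCIC consent | Researcher search alone | Only if searched before release |

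The last two rows contribute to the primary endpoint and are protected only by the timing of the search. The last row is the more exposed, since no central record exists to set against the search.

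**2. Which searches can fall after release?** Searches ran throughout the trial, so many precede the 18-month interview. An attendance shortly before month 18 must first appear in a download and be found unclear before it can be queried. For these, the query falls around or after the interview, when the rule permits unblinding. The exposed part is this late remainder, plus late searches for participants without HSCIC consent.

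**3. How large could the effect be?** The article gives no share of unclear attendances, no share resolved late and no figure to reproduce. All inputs here are assumptions, and there is no true effect.

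- E = 100 candidate attendances per arm; half of the unclear ones are counted on average.
- u = share unclear; d = gap between arms in the share counted among those resolved late; L = share of unclear attendances resolved late.
- Events in FT = E(1 − u) + E·u·(0.5 − L·d/2); events in TAU = E(1 − u) + E·u·(0.5 + L·d/2).
- Apparent HR (FT v TAU) = ratio of events; shift in z = ln(HR) × √(total events)/2; two-sided rejection at 1.96.

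Example with u = 0.3, d = 0.4:
- L = 1: FT 70 + 30 × 0.3 = 79; TAU 70 + 30 × 0.7 = 91; HR = 79/91 = 0.868; shift = ln(0.868) × √170/2 = −0.92; false-positive rate 15.2%.
- L = 1/3: FT 83, TAU 87; HR = 83/87 = 0.954; shift = −0.31; false-positive rate 6.1%.

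| u | d | L = 1: HR, false-positive rate | L = 1/3: HR, false-positive rate |
|---|---|---|---|
| 10% | 10 points | 0.990, 5.1% | 0.996, 5.0% |
| 20% | 20 points | 0.957, 6.0% | 0.985, 5.1% |
| 30% | 20 points | 0.932, 7.5% | 0.977, 5.3% |
| 30% | 40 points | 0.868, 15.2% | 0.954, 6.1% |

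The L = 1 column is an upper bound, since it treats every unclear attendance over 18 months as resolved unblinded. The L = 1/3 column is closer to the mechanism in step 2, but one third is itself an assumption. The article sets the final alpha at 0.047; using it in place of 0.05 lowers the 15.2% to 14.5% and the 6.1% to 5.7%.

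**The case against.** A reader might infer that unblinded researchers decided which attendances counted as self-harm. The article does not support that. It says researchers searched for episode details; it does not say who classified attendances, or that anyone already unblinded to a participant later searched that participant's records. Its example of when researchers could be unblinded, the end of follow-up, is compatible with release after attendance queries were closed.

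The safeguards are also real. For participants linked to HSCIC, the list of attendances comes from a central download whatever the arm, and the detail sought sits in routine hospital notes. Searches were frequent, and Table 1 has hospital attendance collected on an ongoing basis. The interim analysis, due at 86 or more events, was reviewed in July 2013, before recruitment closed that December, so endpoint events were being ascertained during the trial. The Background puts the highest repetition risk in the first year, which leaves fewer first events for the late window.

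These arguments limit the size of the problem, and they rule out the 15% figure as an estimate. They do not remove it. The article attributes to HES the avoidance of preferential collection at particular Trusts, which is a different matter from knowledge of the arm. The full protocol or a SAP may settle the order of searching and unblinding and name the classifier, and their absence here is not a fault. But the release rule is stated explicitly in the article, and as stated it names the wrong milestone.

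**Conclusion.** The point holds as a defect in a stated rule. The release of researcher blinding is narrower than the article's own purpose of unbiased follow-up data, and it permits late searches feeding the primary endpoint to be done unblinded. It is not evidence that primary-endpoint events were ascertained or classified with knowledge of the arm.

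The share affected is unknown. On the assumptions shown, with one third of unclear attendances resolved late, the false-positive rate stays between 5.0% and 6.1%. The bias becomes material only if many attendances are unclear, most are resolved late, and the arms are handled quite differently. The calculation does not separately model participants without HSCIC consent, whose number is not given. The change is worth making because it is inexpensive and protects the primary outcome, not because the likely bias is large.

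**What to change.** Change the trigger in the Follow-up section. A researcher may see or collect a participant's treatment data only after that participant's hospital attendances to 18 months have been searched and their self-harm status recorded and locked. Apply this equally to participants without HSCIC consent. Until the lock, treatment data come from the treating clinicians, family therapists and Clinical Studies Officers whom the section already names.

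Where a participant's researcher is already unblinded, any remaining query should go to a researcher who has not seen that participant's treatment data, if that person already has access to the Trust's records. Research governance requires a Letter of Access from each Trust, so routine cross-site handling should not be assumed to be cheap. Where no such person is available, flag the attendance as resolved unblinded and add it to the sensitivity analysis in Primary endpoint analysis.

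Trial status describes follow-up as nearly but not fully complete, so the latest searches can still be protected. The cost is mainly resequencing, plus a lock for each participant. Some treatment data will arrive later, and in the meantime the trial leans more on clinicians and Clinical Studies Officers; Clinical service engagement describes collection from clinicians as labour-intensive and open to missing data.

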### Intervention

Both therapeutic interventions were delivered within CAMHS, and all participants were treated within their local service. Family therapists were formally linked with specific CAMHS teams to ensure lines of clinical responsibility were clear, and all clinicians in both arms of the trial had access to local child and adolescent psychiatrists if medication or hospitalisation needed to be considered.

### Family therapy

The Family Therapy intervention was based on a modified version of the Leeds Family Therapy & Research Centre Systemic Family Therapy Manual (LFTRC Manual), the development and validation of which was funded by the Medical Research Council (MRC)  to support trials of FT [45]. This manual was updated by the Family Therapy expert members from the Trial Management Group to ensure it was appropriate for work with families following self-harm. Qualified Family Therapists (those eligible for registration with the UK Council for Psychotherapy - UKCP) were appointed specifically to work on the trial. Family therapists worked in teams of 3 or 4 and provided trial FT as a team for a cluster of CAMH services. They received initial training, undertook pilot work and received monthly supervision from the SHIFT Family Therapy leads in each locality. Annual meetings of the trial therapists were organised to ensure ongoing consistency of the treatment approach across all trial sites.

Plans were made for the young people and their families to attend FT sessions of approximately 1¼ hours duration each, delivered over 6 months at approximately monthly intervals but with more frequent initial appointments. This equated to approximately 8 sessions, but there was the expectation that some participants would receive fewer sessions due to drop-out or mutually agreed-upon termination of treatment. Equally, it was anticipated that some might receive more sessions (within the predefined 6-month period, or extending beyond 6 months) where this was deemed clinically appropriate.

Wherever possible, and where consent was provided, sessions were video recorded as this is part of good family therapy practice and facilitates supervision. In addition, this procedure facilitated central review of a selection of sessions to monitor adherence to the manual and allow reporting of this.

### Treatment as usual

TAU was the care offered by local CAMHS teams to adolescents referred following self-harm. This treatment was anticipated to be diverse and involve individual and/or family-orientated work, delivered by a range of practitioners with various theoretical orientations. As SHIFT is a pragmatic trial involving a number of collaborating CAMHS teams, the specification of TAU was not deemed possible or appropriate, although it was expected that CAMHS practitioners would be working in line with best practice as set out in several National Institute for Health and Care Excellence (NICE) guidelines (for example, guidance on self-harm and depression in childhood [46, 47]). TAU thus involved a wide range of treatment techniques and modalities (such as supportive counselling or cognitive behaviour therapy) that were not delivered to the FT group as part of the clinical intervention, unless they became indicated during or after family therapy.

### Contamination

The possibility of cross-arm contamination was considered during the design stage of the trial, with the following points noted and action taken:Different teams of therapists delivered the two interventions in each CAMH service, and the SHIFT family therapists were prohibited (wherever possible) from treating participants in the TAU arm for the duration of the trial. However, in the few cases where this was unavoidable, contamination was recorded and levels will be reported.Due to the nature of appointment scheduling, and the fact that this was family-specific therapy (that is, not a group intervention), there was little opportunity for participants to meet and discuss treatment, so contamination was very unlikely.Any family-orientated clinical interventions in the TAU group were likely to be different from the trial FT intervention, which required adherence to the LFTRC manual, fully-trained family therapists eligible for United Kingdom Council for Psychotherapy (UKCP) registration, therapy delivered in a team context and regular supervision.

### Safety monitoring

Non-serious adverse events were operationally defined in SHIFT as treatment on an emergency outpatient basis (A&E attendance) and re-referral to CAMHS, as these events are expected to occur within the adolescent study population. Deaths and hospital admissions were defined as serious adverse events because, although not as common, they are to be expected in the population being studied.

An independent Data Monitoring and Ethics Committee (DMEC) is scheduled to meet at least annually to review the safety and ethics of the trial during recruitment and follow-up. The DMEC review the number and frequency of hospitalisations and deaths overall and as a consequence of self-harm and could recommend trial suspension or closure if a significantly increased frequency of such events in one or both arms is identified.

### Research governance

The Trial is managed on a day-to-day basis by the Chief Investigator and a core team from the Clinical Trials Research Unit at the University of Leeds. All collaborators, including trial research staff, form the Trial Management Group, which meets on a regular basis to review progress. Independent oversight is provided by the Trial Steering Committee and Data Monitoring and Ethics Committee.

The trial was reviewed and approved by the NHS Research Ethics Committee (REC)  Yorkshire and the Humber - Leeds West (REC reference 09/H1307/20). SHIFT also received R&D approval from all participating CAMHS’ host organisations. For the purposes of collecting routine data from Acute Trusts to inform the primary outcome, the REC agreed that the study was exempt from Site Specific Assessment, but Researchers required Letters of Access from each Trust to access records. Participants could withdraw from further researcher contact, receipt of postal questionnaires or collection of clinical data from CAMHS/Acute Trusts/HSCIC. Withdrawal requests were respected throughout the trial and data were only obtained where valid consent remained in place.

The following organisations gave research governance approval for the study:

5 Boroughs Partnership NHS Foundation Trust

Airedale NHS Foundation Trust

Alder Hey Children’s NHS Foundation Trust

Barnet and Chase Farm Hospitals NHS Trust

Barnet, Enfield and Haringey Mental Health NHS Trust

Bolton NHS Foundation Trust

Bradford District Care NHS Foundation Trust

Bradford Teaching Hospitals NHS Foundation Trust

Calderdale & Huddersfield NHS Foundation Trust

Central Manchester University Hospitals NHS Foundation Trust

Croydon Health Services NHS Trust (formerly Mayday)

Dartford and Gravesham NHS Trust

East London NHS Foundation Trust

Guy’s and St Thomas’ NHS Foundation Trust

Harrogate and District NHS Foundation Trust

Homerton University Hospital NHS Foundation Trust

Hull and East Yorkshire Hospitals NHS Trust

Humber NHS Foundation Trust

Kings College Hospital NHS Foundation Trust

Leeds Community Healthcare NHS Trust

Leeds Teaching Hospitals NHS Trust

Leeds and York Partnership NHS Foundation Trust

Lewisham Healthcare NHS Trust

The Mid Yorkshire NHS Trust

North Lincolnshire and Goole Hospitals NHS Foundation Trust

North Middlesex University Hospital NHS Trust

Oxleas NHS Foundation Trust

Pennine Acute Hospitals NHS Trust

Pennine Care NHS Foundation Trust

### Statistical considerations

#### Power calculation/sample size consideration

The power calculation was based on a minimally important reduction in 18-month repetition rates of self-harm (leading to hospital attendance) from 29 % in participants receiving TAU [48] to 18.8 % in participants receiving FT, that is, a reduction of 35 %. Using a 5 % significance level log-rank test for equality of survival curves, 374 participants per arm were required, with 172 total events, to give 90 % power to detect this reduction in 18 month repetition rates, providing a constant hazard ratio of 1.64. Assuming at most a 10 % loss to follow-up by 18 months for the primary outcome, the total sample size required was 416 per arm, 832 in total.

Although SHIFT is an individually randomised trial, inherent clustering within the data structure (participants nested within therapists) is known to have an impact on power and is related to the level of the intra-cluster correlation coefficient (ICC) and the cluster size. It was expected that the level of clustering would be low - possibly around 0.01 but no higher than 0.05 (due to use of therapy manuals, therapist selection, training, supervision and monitoring). In addition, the number of participants per therapist was expected to be small. In the TAU arm, it was estimated that there would be between eight and 15 therapists available in the team at any one centre, so across the anticipated 15 participating Trusts there would be 120 to 225 therapists available to treat 416 participants. Thus, each therapist would treat between two and four participants (maximum control cluster size of 4). In the FT arm, we estimated that there would be approximately 35 therapists available across all the sites to treat 416 participants; operating in teams of three or four therapists. Within each FT team, each therapist would be the lead for a subset of participants at that site (the other therapists in the team would act as observers and make only a small face to face contribution for those participants). Thus, each FT therapist would have direct contact with approximately 12 participants (maximum intervention cluster size of 12).

The design effect, describing the extent to which the sample size must be increased to obtain the same power as an individually randomised study without clustering, was therefore assumed likely to be no greater than 1.55 (assuming an ICC of 0.05), effectively reducing the sample size from 416 per group to 270 per group and the power from 90 % to around 75 %. If the ICC were as low as 0.01, then the design effect would be 1.11, reducing the sample size to 374 per group and the power to around 85 %. We anticipated the ICC would be towards the lower end of the possible range, and therefore, the trial would still be adequately powered with the sample size planned.

